## Abstract

**Background:**

High blood pressure is an important determinant of cardiovascular disease risk. Treated hypertensives do not attain a risk level equivalent to normotensives. This may be a consequence of suboptimal blood pressure control to which indiscriminate use of antihypertensive drugs may contribute. Indeed the recent ALLHAT[1]study suggests that thiazides should be given first to virtually all hypertensives. Whether this is correct or whether different antihypertensive therapies should be targeted towards different patients is a major unresolved issue, which we address in this study.

The measurement of the ratio of aldosterone: renin is used to identify hypertensive subjects who may respond well to treatment with the aldosterone antagonist spironolactone. It is not known if subjects with a high ratio have aldosteronism or aldosterone-sensitive hypertension is debated but it is important to know whether spironolactone is superior to other diuretics such as bendroflumethiazide in this setting.

**Methods/design:**

The study is a double-blind, randomised, crossover, controlled trial that will randomise 120 hypertensive subjects to 12 weeks treatment with spironolactone 50 mg once daily and 12 weeks treatment with bendroflumethiazide 2.5 mg once daily. The 2 treatment periods are separated by a 2-week washout period. Randomisation is stratified by aldosterone: renin ratio to include equal numbers of subjects with high and low aldosterone: renin ratios.

Primary Objective – To test the hypothesis that the aldosterone: renin ratio predicts the antihypertensive response to spironolactone, specifically that the effect of spironolactone 50 mg is greater than that of bendroflumethiazide 2.5 mg in hypertensive subjects with high aldosterone: renin ratios.

Secondary Objectives – To determine whether bendroflumethiazide induces adverse metabolic abnormalities, especially in subjects with high aldosterone: renin ratios and if baseline renin measurement predicts the antihypertensive response to spironolactone and/or bendrofluazide

**Discussion:**

The numerous deleterious effects of hypertension dictate the need for a systematic approach for its treatment. In spite of various therapies, resistant hypertension is widely prevalent. Among various factors, primary aldosteronism is an important cause of resistant hypertension and is now more commonly recognised. More significantly, hypertensives with primary aldosteronism are also exposed to various other deleterious effects of excess aldosterone. Hence treating hypertension with specific aldosterone antagonists may be a better approach in this group of patients. It may lead on to better blood pressures with fewer medications.

## Background

### Epidemiology

One approach to more effective antihypertensive control would be to target aldosterone antagonists towards patients in whom these drugs are likely to work best. Hyperaldosteronism is characterised by excessive excretion of aldosterone with concomitant suppression of renin associated with hypertension. However, neither aldosterone excretion nor plasma renin activity alone has proved useful in screening for this condition for a variety of reasons. Hiramatsu and colleagues have suggested that the aldosterone: renin ratio may be a useful screening test[2]. Using the aldosterone: renin ratio to find possible cases, Gordon and colleagues reported that hyperaldosteronism was more common than suspected, with 8% of cases referred to his clinic having this condition[3]. A high aldosterone: renin ratio has been found in 15% of a UK hypertension clinic[4] and the general community[5]. There is debate as to whether a raised ratio defines aldosteronism or whether it detects a subgroup of subjects with aldosterone-sensitive hypertension, although subjects with a raised ratio do appear to have genetic differences from those who do not[6]. If further testing is undertaken, 94% of clinic subjects with a raised ratio did not suppress plasma aldosterone with salt loading, a test many regard as diagnostic[4]. However, salt-loading is not without risks[7] and a simple blood test that was able to guide appropriate therapy is an attractive concept.

### Rationale for study

Most subjects with a raised aldosterone: renin ratio do not have distinct metabolic abnormalities. Furthermore, if they are investigated, most do not have adrenal adenomas; instead they have adrenal hyperplasia or even normal sized adrenal glands. While some authorities recommend full investigation and laparoscopic adrenalectomy if excessive aldosterone secretion can be lateralised to one of the glands[8,9], surgery is not without risks and 60% of adrenalectomised subjects require antihypertensive therapy[10]. In addition, those who have a good response to surgery also show a good response to spironolactone[11] and long term drug treatment is safe and effective[12]. Furthermore, there remains some debate about the true distinction between genuine autonomous primary aldosteronism and relative aldosterone excess association with low renin hypertension. The purpose of the proposed study is not to resolve this argument, but instead to answer a pragmatic question about the best treatment of patients with resistant hypertension. There is no argument that patients with a high aldosterone: renin ratio may have resistant hypertension. It is also clear that the number of patients with a high ratio forms a large sub-group of patients with high blood pressure. Aldosterone has deleterious effects on the cardiovascular system and it is possible that patients with hypertension who have a high aldosterone: renin ratio are at particular risk of cardiovascular morbid events. Thus, it is of considerable practical importance to define what treatment provides best blood pressure lowering and cardiovascular protection to these subjects [13-15] In this regard, a recent observational study done by one of the authors provides some evidence that subjects with a raised aldosterone: renin ratio had good anti-hypertensive responses to more usual doses of spironolactone (25–100 mg)[16]. Importantly, the subjects treated with spironolactone had better blood pressure control with fewer antihypertensive drug treatments after spironolactone was commenced.

There is on going debate on the topic of the aldosterone: renin ratio and its role, if any, in subjects with hypertension. It is true that we need better evidence of the practical value of measuring the ratio before we recommend change to current practice and treat patients with spironolactone. A key question is "would such a strategy be better than treating all subjects conventionally with a thiazide diuretic?"

### Rationale for doses of bendroflumethiazide and spironolactone

Previous studies with thiazide diuretics have suggested that the dose-response relationship is shallow. With bendroflumethiazide, the most commonly used thiazide in the UK, 2.5 mg is almost as effective as 5 mg and as a consequence very few physicians use the higher dose. In essential hypertension, a similar dose-response relationship is true for spironolactone but higher doses of spironolactone may reduce BP more in those with high aldosterone: renin ratios. In one sense, the ideal comparison would be between exactly equipotent doses of these two drugs. However, the critical question is whether the efficacy of the usually prescribed doses of these drugs is predicted by the aldosterone: renin ratio. This is the pragmatic question that is relevant to day-to-day clinical practice. In order to test this hypothesis, it is not necessary for the doses employed to be exactly equipotent. For this reason we have chosen 50 mg of spironolactone, to be compared with 2.5 mg of bendroflumethiazide, the most commonly used doses of each drug.

### Rationale for choice of subjects

In an ideal study, subjects would be untreated at entry. However, patients with high aldosterone: renin ratios tend to have resistant hypertension. For ethical reasons, it is not possible to discontinue anti-hypertensive therapy in such individuals. In addition, in a pragmatic study allowing drug treatment at entry will result in the study population being more representative of the true patient population. We recognise that it is necessary to restrict the types of drug therapy used for the duration of the trial to maximise the information gained from the randomised arms. Although some drugs may independently affect renin and aldosterone, in a crossover trial these effects should be balanced. Thus, subjects taking medication at screening continue on or are changed to standard open drug therapy to control blood pressure in the following order of preference: alpha-blockers, centrally acting drugs, calcium channel blockers, cardio-selective beta blockers and (exceptionally) ACE inhibitors and angiotensin receptor blockers. Allowing subjects into the study who are hypertensive on drug therapy enriches the study population with cases of resistant hypertension. We accept that this may bias the study towards a secondary care type of population, but we believe that many such patients do exist in primary care, albeit in smaller numbers and that the study will still be relevant to that setting.

## Methods/design

### Study design

The study is a double-blind, randomised, crossover, controlled trial that will randomise 120 hypertensive subjects to 12 weeks treatment with spironolactone 50 mg once daily and 12 weeks treatment with bendroflumethiazide 2.5 mg once daily. The 2 treatment periods are separated by a 2-week washout period. Investigators and subjects do not know the order of the treatment periods, which is according to a computer generated randomisation list. Randomisation is stratified by aldosterone: renin ratio to include equal numbers of subjects with high and low aldosterone: renin ratios. This is necessary as in an unselected population, only 15% of subjects will have an aldosterone: renin ratio > 750.

### Study population

Potential study subjects with mild-moderate hypertension are identified from clinic patients or from community treated patients.

### Inclusion/exclusion criteria

#### Screening

Written informed consent is obtained prior to carrying out screening procedures. Potential subjects are assigned a subject number. Antihypertensive therapy may not be necessarily be discontinued[17] but may be in some cases, or it may be adjusted if necessary. Specifically, potential subjects on spironolactone, and for whom, in the opinion of the investigator, there is no compelling indication not to discontinue this for the purpose of taking part in the study, may have this drug discontinued 3 months prior to entry, provided full written informed consent is obtained. Diuretics should be discontinued for a minimum of 2 weeks prior to entry and also beta-blockers, where possible. Alternative antihypertensive treatment may be substituted.

Medical history, concomitant conditions and medications are recorded and a physical examination carried out. Height and weight are measured. Blood pressure is measured using the OMRON 705CP[18]. The mean of three readings is taken after two minutes rest in the sitting position with the arm supported at the level of the heart. A 12-lead ECG and clinical laboratory tests including urinalysis, blood biochemistry and haematology are carried out. Blood samples for measurement of plasma aldosterone and plasma renin activity are taken (after 5 min sitting quietly).

Subjects undergo ambulatory blood pressure monitoring for 26 hours using Spacelabs 90207 monitor. This is set to take readings every 15 minutes during daytime (0800 h–2159 h) and every 30 minutes during night time (2200 h–0759 h). To be considered evaluable, the ABPM report must contain at least 24 hours data, including at least one valid reading for every hour during daytime and every 2 hours during night time. To fulfil the inclusion criteria, mean daytime systolic BP on screening ABPM must be at least 140 mmHg.

#### Randomisation

Blood samples for aldosterone and renin, from subjects who fulfil all other inclusion criteria, are analysed by a central laboratory.

#### Stratified randomisation

The aldosterone: renin ratio calculated by the central laboratory is used to stratify subjects. For the purposes of this study subjects must have either a high aldosterone: renin ratio > 750 with a plasma aldosterone > 250 pmol/l or a low aldosterone: ratio < 300 with plasma renin activity <10 ng/ml/h.

#### Follow-up visits

Randomised subjects are seen at one week, four weeks, eight weeks and twelve weeks during each treatment phase. On each occasion blood pressure is measured using OMRON 705CP and a safety blood sample taken for potassium, magnesium and creatinine. Subjects are also asked if they have experienced adverse events or any changes in concomitant medication. Investigators may repeat ambulatory blood pressure monitoring at follow-up visits if they wish to. These data will not be used in the analysis.

On the penultimate day of each treatment period subjects have Omron BP measurements prior to fitting an ambulatory blood pressure monitor. On their return 26 hours later, on their final day of treatment, subjects again have Omron BP measurements. The mean of these two mean blood pressures is a secondary endpoint of the study. Mean daytime ambulatory blood pressure and mean night time blood pressure are also secondary blood pressure endpoints. The primary endpoint is mean 24-hour blood pressure.

At the end of the study, subjects are commenced or continued on standard anti-hypertensive therapy and followed up as per usual clinical care.

### Safety considerations

#### Assessments

Safety assessments consist of monitoring and recording all adverse events (AEs) and serious adverse events (SAEs), measurement of blood pressure and heart rate, monitoring of blood biochemistry, ECG recordings and physical examination if indicated.

#### Uncontrolled blood pressure

If blood pressure is uncontrolled investigators may use their discretion and add further antihypertensive medication in the following order of preference: alpha-blockers, centrally acting drugs, calcium channel blockers, cardio-selective beta blockers and (exceptionally) ACE inhibitors and angiotensin receptor blockers. A log of all medication taken during the study is kept for each subject.

#### Symptomatic hypotension

If the investigator suspects that a subject is suffering symptomatic hypotension, then open-label anti-hypertensive medication can be withdrawn or study medication can be reduced to one capsule every second day.

#### Hypokalaemia/hyperkalaemia

Subjects who develop hypokalaemia (K^+ ^< 3.5 mmol/l) are given slow release potassium supplementation 600 mg three times daily. If hypokalaemia is deemed severe (K^+ ^< 3 mmol/l) study medication is discontinued for three days or until K^+ ^is > 3.5 mmol/l whereupon study medication is restarted at one capsule taken every second day along with potassium supplementation. Subjects who subsequently develop hypokalaemia have study medication withdrawn. Similarly, study medication is stopped temporarily and restarted at half dosage if plasma K^+ ^> 5.5 mmol/l.

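### The restart rule after severe hypokalaemia joins a three-day limit and a potassium level with *or* and does not say which governs, so its wording permits restart before potassium has recovered

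*Protocol article*

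**What the plan says.** The rule is in the protocol article, Safety considerations, under Hypokalaemia/hyperkalaemia. Hypokalaemia is defined as potassium below 3.5 mmol/l and is treated with slow-release potassium, 600 mg three times daily. Below 3 mmol/l it counts as severe, and "study medication is discontinued for three days or until" potassium is above 3.5 mmol/l. The restart is at reduced dose: "whereupon study medication is restarted at one capsule taken every second day along with potassium supplementation". The next sentence adds a backstop: "Subjects who subsequently develop hypokalaemia have study medication withdrawn".

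Two other sections bear on the rule. Assessments lists, among the safety measures, "monitoring of blood biochemistry, ECG recordings and physical examination if indicated". Follow-up visits sets the routine schedule: "Randomised subjects are seen at one week, four weeks, eight weeks and twelve weeks during each treatment phase", with the instruction "On each occasion blood pressure is measured using OMRON 705CP and a safety blood sample taken for potassium, magnesium and creatinine".

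**The concern.** The sentence gives two ways for the interruption to end, one by the calendar and one by a laboratory value, and connects them with *or*. It does not say whether the earlier or the later applies, or whether the investigator may choose. Taken at its word, three days off drug is enough, whatever the potassium level then is.

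What is at stake is patient safety and consistency between investigators. Two investigators following the same sentence could resume the drug at different potassium levels, one of them before the severe hypokalaemia has been corrected. The setting makes the event foreseeable: one of the two treatments is a thiazide, a secondary objective asks whether it causes adverse metabolic effects, especially in high-ratio subjects, and equal numbers of high- and low-ratio subjects are recruited. Investigators do not know the order of treatments, so they cannot rely on knowing which drug they are restarting. They depend on the written rule.

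**Working it through.** The document gives no figure to reproduce, and no sample-size or analysis quantity enters. The check is a reading of the rule's logic.

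**Inputs**, all from Hypokalaemia/hyperkalaemia: stop when K+ < 3 mmol/l; time condition T = three days elapsed; potassium condition P = K+ > 3.5 mmol/l; restart at one capsule every second day with potassium supplementation.

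**Step 1. The rule as written: restart if T or P.**

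| Three days elapsed (T) | K+ > 3.5 mmol/l (P) | Restart under *T or P* | Restart if P is required |
|---|---|---|---|
| yes | yes | yes | yes |
| yes | no | **yes** | **no** |
| no | yes | yes | yes |
| no | no | no | no |

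The two columns differ only in the second row: three days have passed and potassium is still at or below 3.5 mmol/l. Nothing in the wording keeps that row from including values still below 3 mmol/l, the level that triggered the stop.

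**Step 2. The readings the sentence allows.**

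- Whichever comes first: the second row is permitted.
- Three days, extended if necessary until recovery: the second row is excluded.
- Investigator's choice of condition: the second row is permitted.

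The second reading is the likeliest, because the word introducing the restart comes straight after the potassium level. The sentence does not rule out the other two.

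**Step 3. The backstop.** The following sentence withdraws the drug from subjects in whom hypokalaemia develops after the restart. That presupposes recovery in between, which again points to the second reading. For the same reason it does not clearly reach a subject restarted without recovery, whose hypokalaemia continued and did not develop anew. Under the literal rule, a potassium of, say, 3.2 mmol/l would allow restart on day three, yet the same value arising after a restart would require withdrawal.

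**Step 4. The rest of the document.** Assessments provides for biochemistry monitoring in general and sets no restart condition. Follow-up visits fixes routine samples at weeks 1, 4, 8 and 12 and does not bar extra ones. Neither section says which of the two conditions governs.

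**The case against.** The strongest reply is that no careful investigator would read the sentence literally. The order of the words, and the next sentence's assumption of recovery, both suggest restart after correction; a reading that sets adjacent sentences against each other is the weaker one. This stands as evidence of intent. It does not remove the ambiguity: if potassium alone governs, the three days have no clear function, and a safety rule should not depend on inferring what was meant.

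A second reply is that repeat sampling is already implied. Consecutive routine samples are 4 − 1 = 3, 8 − 4 = 4 and 12 − 8 = 4 weeks apart, so after a stop prompted by a routine sample, recovery can be established promptly only by sampling off schedule. This stands too. A reader might infer from the visit schedule that a restarted subject would go weeks on drug with no potassium check. The document does not support that: it names a potassium level as an end to the interruption, provides for biochemistry monitoring and permits extra samples. A long unmonitored gap would come from an investigator not rechecking a potassium below 3 mmol/l; it does not follow from the word *or*.

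A third reply is that a journal article leaves operational detail to the full protocol. That is right for the timing of rechecks, and their absence is not criticised here. But the article does state a stop-and-restart rule with numerical limits, and the point concerns how that rule is worded.

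Finally, the mitigation is real. Potassium supplements are given, the dose is halved, later hypokalaemia leads to withdrawal, and severity is left partly to clinical judgement. These lessen the harm but do not settle which condition governs.

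**Conclusion.** The point holds as a minor ambiguity in a safety rule. The sentence does not say whether the time limit or the potassium level decides, so its wording allows restart after three days with potassium at or below 3.5 mmol/l, and the withdrawal sentence does not clearly catch a subject who never recovered.

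A reader might go further and infer that the trial deliberately chose to restart uncorrected subjects. The text does not support that; recovery before restart is the more natural intention. The point is limited to hypokalaemia.

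No size can be put on it. The article does not say how often severe hypokalaemia is expected; the assumption here is that few subjects would be affected and that many investigators would recheck potassium anyway. No effect on the primary analysis is claimed.

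**What to change.** Make the potassium level the sole condition for restart and let three days serve only as a suggested time to recheck. For example: after a potassium below 3 mmol/l, the study drug stays stopped until a repeat sample (for instance at about three days) shows K+ > 3.5 mmol/l; it then resumes at one capsule on alternate days with potassium supplementation.

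This removes the second row of the table. It also gives the withdrawal sentence a clear meaning, since every restarted subject will have recovered first. The cost is a one-sentence change, an occasional extra potassium sample, and a longer interruption of study drug for the few subjects whose potassium is slow to correct.

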### Endpoints

#### Primary endpoint

The primary endpoint is the difference in mean 24-hour systolic ambulatory blood pressure recorded at the end of each 12-week treatment period.

#### Secondary endpoints

Secondary endpoints include the differences between the following measurements taken at the end of each 12-week treatment period

• Mean 24 hour diastolic ambulatory blood pressure

• Mean daytime ambulatory blood pressure

• Mean night time ambulatory blood pressure

• Mean clinic blood pressure defined as mean of mean clinic BPs on both penultimate and final days of treatment periods

• Clinical biochemistry measurements of plasma potassium (K^+^), magnesium (Mg^2+^), creatinine, triglycerides, cholesterol and HDL cholesterol

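### The potassium endpoint is read only at week 12, after the protocol's own potassium rules may have acted, so it understates the drugs' effect on potassium

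*Protocol article*

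**What the plan says.** The abstract (Methods/design) gives as a secondary objective: "To determine whether bendroflumethiazide induces adverse metabolic abnormalities, especially in subjects with high aldosterone: renin ratios".

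Under Secondary endpoints, the timing is fixed for the whole list: "Secondary endpoints include the differences between the following measurements taken at the end of each 12-week treatment period". The list includes "Clinical biochemistry measurements of plasma potassium" together with magnesium, creatinine and three lipid measures.

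Under Analyses, each outcome becomes one number per patient, the bendroflumethiazide value minus the spironolactone value. These differences are compared between the ratio groups by t-test. Nothing is said there about potassium treatment given during the period.

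Under Follow-up visits: "Randomised subjects are seen at one week, four weeks, eight weeks and twelve weeks during each treatment phase", each time with "a safety blood sample taken for potassium, magnesium and creatinine".

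The section Hypokalaemia/hyperkalaemia acts on those samples in steps:
- Below 3.5 mmol/l, patients "are given slow release potassium supplementation 600 mg three times daily".
- Below 3 mmol/l, study medication is interrupted, "whereupon study medication is restarted at one capsule taken every second day along with potassium supplementation".
- If hypokalaemia then recurs, study medication is withdrawn.
- Above 5.5 mmol/l, study medication is stopped for a time and resumed at half dosage.

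**The concern.** The outcome variable triggers its own correction before it is measured. Three visits (weeks 1, 4 and 8) come before the endpoint, and at each of them a patient with an out-of-range value can be supplemented, put on a reduced dose or, on recurrence, taken off study drug. The week-12 comparison then answers what potassium looks like under protocol management. The objective asks what the drug does.

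At stake are the mean potassium difference between the drugs, the number of patients seen to be out of range, and the comparison between ratio groups that the objective singles out. The primary blood pressure endpoint is not part of this point.

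**Working it through.** **What the plan gives.** There is no mean, SD, incidence or expected drug effect for potassium, so there is no potassium figure to reproduce. The sample size is for blood pressure and is not in dispute. With SD 11 and difference 6, the between-group formula gives 2 × (1.960 + 0.842)² × 11²/6² = 52.8, so 53 by the normal formula and 54 with the t distribution. The plan has 54, and 54/0.9 = 60.

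**Direction of the mean.** Write D for bendroflumethiazide minus spironolactone potassium, expected to be negative. Supplementing or reducing the dose for low values on bendroflumethiazide raises the first term. Stopping or halving for high values on spironolactone lowers the second. Each moves D toward zero, so observed D = true D + a, with a > 0. This assumes that low values arise mainly on bendroflumethiazide and high values mainly on spironolactone. Corrections in the opposite period would work the other way.

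**Simple size (assumed inputs, bendroflumethiazide side only).** If a share p is corrected by r mmol/l before week 12, the mean fall is understated by p × r. With p = 20% (10% to 30%) and r = 0.5, this is 0.10 mmol/l (0.05 to 0.15). Of 54 patients, 54 × 0.20 = 10.8, about 11 (5 to 16), would have been corrected.

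**Simulation (assumed inputs).** The supplementation, dose-reduction and withdrawal rules were applied at weeks 1, 4 and 8 and potassium was read at week 12, with 400,000 simulated patients per row. Assumed SDs: baseline 0.3, individual response 0.15, visit-to-visit 0.15. Values are in mmol/l; BFZ is bendroflumethiazide and SPI is spironolactone.

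| Baseline | BFZ effect | SPI effect | Supplement effect | D without rules | D with rules | Shrinkage | <3.5 at week 12 on BFZ, without rules | with rules | ever <3.5 on BFZ, with rules |
|---|---|---|---|---|---|---|---|---|---|
| 4.2 | −0.3 | +0.3 | +0.3 | −0.60 | −0.53 | 11% | 14% | 5% | 24% |
| 4.0 | −0.4 | +0.3 | +0.4 | −0.70 | −0.48 | 31% | 39% | 9% | 56% |
| 3.8 | −0.5 | +0.3 | +0.4 | −0.80 | −0.42 | 48% | 71% | 18% | 84% |
| 3.8 | −0.5 | +0.4 | +0.6 | −0.90 | −0.37 | 59% | 71% | 6% | 84% |
| 3.6 | −0.5 | +0.4 | +0.5 | −0.90 | −0.34 | 62% | 86% | 16% | 94% |

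Shrinkage is from unrounded values. Two cautions apply:
- The last row is a stress case. With baseline 3.6 and SD 0.3, (3.5 − 3.6)/0.3 = −0.33, so about 37% start below 3.5 before any drug.
- The last column partly reflects four chances to cross a threshold. The effect of the rules is seen by comparing week 12 without and with them.

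**Ratio-group contrast.** The contrast (high minus low) moves by a(high) − a(low). The third row as the high-ratio group and the first as the low-ratio group give a true contrast of −0.80 − (−0.60) = −0.20 and an observed one of −0.42 − (−0.53) = +0.11, a change of sign. That pairing is a choice. Hyperkalaemia was almost absent in these runs (at most 0.8% ever above 5.5 on spironolactone), and its correction also adds to a. If a were 0.05 in the high-ratio group and 0.15 in the low-ratio group, the contrast would move by −0.10, toward a larger apparent excess at high ratios. With the values exchanged it would move by +0.10.

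**The case against.** The strongest reply has four parts.

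**The harm is not lost.** Potassium is sampled at every visit, adverse events and blood biochemistry are monitored (Safety considerations, Assessments), and a medication log is kept (Uncontrolled blood pressure). The endpoint list is introduced as non-exhaustive, and tabulating potassium events is routine in an analysis plan. This stands as far as it goes. A reader might infer that the trial would report no potassium problem; nothing in the document says that safety data would go unreported. But the article does fix the endpoint's timing and the subtraction, and no endpoint it lists uses the earlier values.

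**The rules are stepwise.** A reader might take any value below 3.5 to mean dose reduction or withdrawal. It does not: values from 3.0 to 3.5 lead to supplements only, with study drug continued. A first fall after week 8 reaches week 12 uncorrected. Hence it is also wrong to say that cases vanish at week 12; 5% to 18% remain below 3.5 in the simulation.

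**Potassium is one of six biochemistry measures.** Supplements do not directly correct the other five, though reduced dosing or withdrawal lowers exposure for all of them. The charge that metabolic harm as a whole is hidden is too broad.

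**Potassium under management is a legitimate measure in a pragmatic trial.** Agreed, and it should be kept. It answers a different question from the one in the objective, and should be labelled so.

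**Conclusion.** The point holds for potassium. Read at week 12 only, after rules that can act at three earlier visits, the endpoint understates the drugs' effect on mean potassium and under-counts threshold events. The direction for the mean rests on low values arising mainly on bendroflumethiazide and high values mainly on spironolactone.

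The size is unknown. All figures rest on assumed inputs: 11% shrinkage in the mildest case and 62% in a stress case, or 0.05 to 0.15 mmol/l by the simple calculation. In the mildest case the loss in the mean is modest.

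A reader might go further and conclude that the ratio-group contrast is biased toward no harm at high ratios. The document does not support that. High potassium on spironolactone is corrected too, and nothing stated shows which correction dominates in which group. The contrast may be distorted in either direction.

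This is a secondary endpoint that answers its stated objective poorly. It should be changed, and the change is cheap.

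**What to change.** Keep the week-12 difference and label it as potassium under protocol management. For the metabolic objective, add two separate secondary endpoints, each scored over all visits of a treatment period:

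- **Hypokalaemia:** potassium below 3.5 mmol/l (also reported below 3.0), or supplementation, dose reduction or withdrawal for low potassium.
- **Hyperkalaemia:** potassium above 5.5 mmol/l, or interruption or dose reduction for high potassium.

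Count an intervention in the period in which it began. Analyse each endpoint as a paired binary outcome with a period term, for example by conditional logistic regression, and include a treatment-by-ratio-group interaction. McNemar tests within each ratio group would neither adjust for period nor test the contrast.

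Do not pool the two directions. A patient with low potassium on one drug and high potassium on the other would count as an event in both periods and drop out as a concordant pair, so opposite harms could cancel.

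Lowest and highest potassium per period may be reported as supportive. The last value before intervention should not be the main mean analysis: it selects the readings that crossed a threshold and compares different weeks across periods.

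The cost is two more derived variables from samples and a medication log already planned. With no potassium incidence stated, the power of the interaction is unknown, so report it with its confidence interval. The clinical potassium rules stay as they are.
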